## Abstract

**Background:**

The Binge Eating Genetics Initiative (BEGIN) is a multipronged investigation examining the interplay of genomic, gut microbiota, and behavioral factors in bulimia nervosa and binge-eating disorder.

**Methods:**

1000 individuals who meet current diagnostic criteria for bulimia nervosa or binge-eating disorder are being recruited to collect saliva samples for genotyping, fecal sampling for microbiota characterization, and recording of 30 days of passive data and behavioral phenotyping related to eating disorders using the app *Recovery Record* adapted for the Apple Watch.

**Discussion:**

BEGIN examines the interplay of genomic, gut microbiota, and behavioral factors to explore etiology and develop predictors of risk, course of illness, and response to treatment in bulimia nervosa and binge-eating disorder. We will optimize the richness and longitudinal structure of deep passive and active phenotypic data to lay the foundation for a personalized precision medicine approach enabling just-in-time interventions that will allow individuals to disrupt eating disorder behaviors in real time before they occur.

**Trial registration:**

The ClinicalTrials.gov identifier is NCT04162574. November 14, 2019, Retrospectively Registered.

## Background

Bulimia nervosa (BN: lifetime prevalence of 1.5% in women and 0.5% in men) and binge-eating disorder (BED: lifetime prevalence of 3.5% in women and 2% in men) are common debilitating eating disorders [1]. BN is marked by uncontrollable eating episodes coupled with compensatory behaviors, whereas BED includes similarly defined binge episodes only in the absence of regular compensatory behaviors. Both disorders are highly heritable (41–82% [2–7]), carry high psychiatric and somatic comorbidity, and have high medication and healthcare utilization, whether or not comorbid obesity is present [8–11]. Suicide risk is significantly elevated in both disorders [12].

The Binge Eating Genetics Initiative (BEGIN) is a multipronged research study that 1) examines the interplay of genomic, gut microbiota, and behavioral factors to explore etiology and develop predictors of risk, course of illness, and response to treatment in BN and BED; and 2) optimizes the richness and longitudinal structure of deep passive and active phenotypic data to lay the foundation for a personalized precision medicine approach enabling just-in-time interventions that will allow individuals to disrupt eating disorder behaviors in real time before they occur.

### Genomics

Despite their prevalence and the attendant personal and social costs, research into the genetic underpinnings of BN and BED is essentially absent. BEGIN represents the first contribution to a global effort to amass an adequate sample size to conduct a genome-wide association study of BN and BED in collaboration with the Eating Disorders Working Group of the Psychiatric Genomics Consortium (PGC-ED). The PGC-ED has rapidly advanced the study of the genomics of anorexia nervosa [13, 14] identifying eight significant loci and reporting a panel of genetic correlations suggesting that anorexia nervosa may have both psychiatric and metabolic etiological underpinnings. BEGIN will further the mission of the PGC-ED by launching a parallel investigation into BN and BED.

### Intestinal microbiota

Inspired by reports of associations between enteric microbes, host metabolism, and host behavior [15–17] along with reported differences between gut microbiota composition from patients with anorexia nervosa and healthy individuals [18–25], we have incorporated the study of the intestinal microbiota into BEGIN. In addition to characterizing the biogeography of the human microbiome (cumulative genomes of the microbiota) of BEGIN participants, our analyses will identify associations between genes and microbial composition in BN/BED. The intention is to better understand the biological mechanisms of these illnesses in an effort to help identify potential drug targets and opportunities for novel interventions.

### Deep phenotyping

We are capturing real-time longitudinal digital phenotypic data on individuals with BN/BED that reflect the true complexity of human behavior. Using Apple Watch and iPhone devices, we are collecting *active* data on binge-eating, purging, nutrition, mood, and cognitions with a widely-used cognitive-behavioral based eating disorder app *Recovery Record* [26] and *passive* sensor data via native applications collected over a 30-day period. We will combine active *Recovery Record*-based measures and passively collected, continuous, sensor-based measurements of autonomic nervous system (ANS) activity and actigraphy to characterize patterns of when and where individuals are more/less likely to binge and/or purge in their daily lives. Finally, across and within individuals, we will identify low-risk and high-risk passive data patterns that will facilitate the prediction of transitions to high risk states signaling impending binge or purge episodes (time-stamped by active app monitoring). This work has the potential to transform the standard of care for BN and BED by transcending current cognitive-behavioral therapy (CBT) approaches typically dependent on retrospective self-report and giving patients a tailored tool that will help them intervene when they need help the most.

## Method

### Specific aims genomics and microbiota

In 1000 individuals with BN/BED, we will,

Aim 1: Contribute genomic data to the next genome-wide association study (GWAS) conducted by the Eating Disorders Working Group of the Psychiatric Genomics Consortium (PGC-ED) of BN/BED.

Aim 2: Comprehensively characterize the biogeography of the human microbiome using high-throughput sequencing of the microbial 16S rRNA gene and shallow shotgun sequencing.

Aim 3: Employ novel and develop new analytic methods to integrate GWAS, gut microbiota, and phenotypic data that will result in predictive algorithms that index risk, course of illness, severity, disordered eating episodes, and treatment response.

### Specific aims digital longitudinal phenotyping

Aim 1: Conduct longitudinal deep phenotyping of 1000 individuals with BN/BED using *Recovery Record* and Apple Watch.

Aim 2: Predict the occurrence of binge eating and purging (vomiting) episodes in individuals with BN/BED using passive sensor data.

Aim 3: Test theoretically derived regulatory models of binge eating and purging behaviors as reflected in differences in temporal patterns.

Aim 4: Refine our capacity to predict binge and purge episodes by augmenting passive data with contextual factors collected by *Recovery Record*.

### Participants

We are recruiting 1000 individuals with BN or BED.

### Inclusion criteria

Currently meets Diagnostic and Statistical Manual for Mental Disorders -5th Edition (DSM-5 [27]) criteria for BN or BED (confirmed via validated questionnaire in screening instrument—see Measures)Resident of USAll sexesAge 18–45 yearsReads, speaks EnglishExisting iPhone user with iPhone 5 or laterWilling/able to wear Apple Watch for entire study periodWilling/able to use *Recovery Record* for the entire study periodProvides informed consent to have activity and self-reported *Recovery Record* data harvestedAmbulatory.

### Exclusion criteria

Currently pregnant or breastfeedingBariatric surgery due to the impact on eating patterns, including the following: (Roux-en-Y gastric bypass, laparoscopic adjustable gastric banding, sleeve gastrectomy, duodenal switch with biliopancreatic diversion, gastric balloon, AspireAssist)Current use of hormone therapyInpatient treatment or hospitalization for eating disorders in the 2-weeks prior to study enrollmentSuicidality at screeningAntibiotic or probiotic use in the past 30 days (related to fecal sampling).

## Recruitment

We are recruiting cases nationally from diverse geographical, socioeconomic, racial, and ethnic backgrounds via *Recovery Record*, social media and National Eating Disorders Association. Specifically, we launch tweets and Facebook posts that direct potential participants to the BEGIN url https://www.med.unc.edu/psych/eatingdisorders/research/participate-in-a-study/begin-study/ where they can take a preliminary screen. In addition, *Recovery Record* pushes notifications about BEGIN to users. Recruitment flow is detailed in Fig. 1.

**Fig. 1 Fig1:**
[figure not shown]
BEGIN study recruitment and sampling flow

### Procedure

Informed consent is obtained digitally via the *Recovery Record* app. Participants complete an eating disorders diagnostic questionnaire. Those who screen case positive and meet all inclusion criteria are offered the opportunity to participate in the full study (with a second digital informed consent). All responses to questionnaires are encrypted and sent to a secure research server at the UNC Sheps Center for Health Services Research using secure transfer methodologies, who compile and house the data in servers specifically designed for Protected Health Information. Data are de-identified (Sheps Center maintains the key to match records). Study data from *Recovery Record* and the Apple Watch are maintained by *Recovery Record* and only includes passive and active sources necessary for analyses, minimizing exposure of protected health information. To ensure that a high level of security is maintained, data transfer from *Recovery Record* occurs with end-to-end encryption and authentication protocols. Records are only identified with a second study number that can be linked using the data from the Sheps Center. Eligible participants are mailed a package containing a description of the study, saliva collection kit, microbiome collection kit, and an Apple Watch. Saliva kits are returned directly to RUCDR Infinite Biologics where they are stored awaiting DNA extraction and genotyping. In Phase 1, participants returned microbiome kits to uBiome for sequencing; in Phase 2, kits are returned to the [name] lab. Barcodes ensure accurate identification and coordination with phenotypic data. After enrollment and completion of the baseline survey, participants use the Apple Watches and *Recovery Record* for 30 days and complete midpoint and end-of-study surveys at 14 days and 30 days post-enrollment, respectively, to track progress of eating disorder pathology, including binge eating and purging behaviors.

### Measures

#### Deep Phenotyping

Using the *Recovery Record* app and the Apple Watch over a 30-day period for each individual, we conduct active and passive data capture to fully characterize disordered eating behaviors, physical activity, nutrition, gastrointestinal distress, sleep, and heart rate. This generates exceptional data to enable deep characterization of the course of BN/BED. We expect that the likelihood of an event (i.e., binge/purge) will decrease over the course of 30-days and build this expectation into our statistical models. We further expect that although the likelihood of events will change over time, the dynamics of the events will not. These data can be broken down into four categories. First, self-report questionnaires are collected consisting of scales well established to relate to BN and BED (see Self-report questionnaires), measured prior to enrollment or three times across the study. Second, stratified sample intensive measurements consisting of daily mood and meal records are measured 6 times daily. Third, event contingent intensive measurements ask participants to log binge and purge episodes. Finally, continuous passive data collection captures real-time physiological and movement data. These different data will be integrated through multilevel modeling and systems continuous time modeling procedures [28, 29].

#### Active data collection

##### Self-report questionnaires

All BEGIN study participants are screened for eligibility and consented using the *Recovery Record* iPhone app, which is free for users to download and is HIPAA compliant (www.recoveryrecord.com). All questionnaires are completed from within the *Recovery Record* app.

##### ED100K [30]

The ED100K questionnaire is a self-report, eating disorders assessment based on the Structured Clinical Interview for DSM-5, Eating Disorders Module, administered prior to enrollment. Items assess DSM-5 criteria for anorexia nervosa, BN, BED, and other specified feeding and eating disorders. The ED100K-v1 was found to be a valid measure of eating disorders and behaviors [30]. Positive predictive values indicating that among those who had a positive screening test, anorexia nervosa Criterion B, Criterion C, and binge eating ranged from 88 to 100%. Among women who had a negative screen, the probability of not having these criteria or behaviors ranged from 72 to 100%. The correlation between questionnaire and interview for lowest illness-related BMI was *r* = 0.91.

##### Eating disorders examination questionnaire (EDE-Q) [31]

The EDE-Q is a widely used, validated questionnaire capturing eating disorders pathology, including the frequency and severity of binge episodes. The EDE-Q is administered at baseline, midpoint, and endpoint of the 30-day period.

##### The Patient Health Questionnaire (PHQ-9) [32]

Is a 9-item, self-administered version of the PRIME-MD diagnostic instrument for common mental disorders. The nine items are based on the nine DSM-IV criteria for major depressive disorder and are scored as “0” (not at all) to “3” (nearly every day). The PHQ-9 has been found to be a reliable and valid measure of depression severity. The PHQ-9 is administered at baseline, midpoint, and endpoint of the 30-day period.

##### The Generalized Anxiety Disorder 7 (GAD-7) [33]

Is a 7-item, self-report questionnaire to screen for generalized anxiety disorder. Each symptom is scored on a 3-point scale: “not at all” (0), “several days” (1), or “more than half the days” (2). Items are then summed to create a symptom severity score. The GAD-7 is a reliable and valid measure of anxiety. The GAD-7 is administered at baseline, midpoint, and endpoint of the 30-day period.

##### ADHD self-report scale (ASRS) [34]

Is an 18-item questionnaire that assess symptoms associated with attention-deficit/hyperactivity disorder. Items are scored on a 5-point scale. The assessment has high internal consistency and validity [35]. The ASRS is administered at baseline.

##### Rome III [36]

To assess adult GI symptoms of the stomach and intestines, the relevant section (items 17–67) of the ROME III is administered at baseline.

#### Stratified sampled intensive measurements

##### Daily mood and meal records

These data are collected inside the *Recovery Record* iPhone app that primarily targets adherence to meal monitoring tasks. Participants are prompted with a push notification six times per day corresponding to meal and snack times to complete an evidence-based CBT-style question set (what was eaten, with whom, where, and what behaviors were used) in addition to optional symptom-focused questions including current emotional state, urges to engage in eating disorder behaviors, sleeping patterns, hunger levels, gastrointestinal problems, and intrusive thoughts.

#### Event contingent intensive measurements

##### Binge and purge records

Participants are instructed to launch the *Recovery Record* Apple Watch app if they have experienced a binge or purge episode (Fig. 2). Action buttons are used to quickly identify the relevant symptom and how long ago it occurred, with response options in five-minute increments ranging from “Right now” to “30 mins ago”. If an urge to engage in a behavior is identified, participants are additionally asked to rate the urge strength with response options: “Not at all”, “Slight”, “Moderate”, “Strong”, and “Overbearing”. Actively monitored mood, meal, binge and purge records and their respective timestamps are collected on the Recovery Record platform and shared with the research team via encrypted authenticated TLS. Ecological momentary assessment-based logging has shown moderate to strong concordance with retrospective self-report of binge eating and purging [37].

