#### Digital longitudinal phenotyping aims

Our dynamic systems approach capitalizes on a combination of the passive and active data collection to address all three of the longitudinal phenotyping aims. Each stable state can be thought of as having homeostatic properties that are reflected in associations between different levels of derivatives (i.e., change in value with respect to time). For example, the relationship between changes in heart rate from one moment to the next and values of heart rate at the previous moment characterize how heart rate fluctuates homeostatically about a “set point.” This set point represents the heart rate value to which the individual’s body returns when the person is at rest [43]. Not only does this association characterize the homeostatic heart rate value itself but also the rate of return to the set point when a person’s heart rate is perturbed (i.e., experiencing distress prior to a binge/purge episode, physical load creating during exercise, etc.). Higher order derivatives and accounting for more variables simultaneously allows for testing more complex homeostatic patterns (e.g., cycles), while including this concept of rate of return to set point (i.e., systemic stability).

Aim 2 will be tested by first depicting the dynamics that lead up to a binge or purge event in a multilevel model. Aim 3 will be addressed by depicting the dynamics once a binge or purge event has occurred. In this case, analyses will focus on the 2 h after binge/purge events (but not within an hour of a future event), again modeling changes in heart rate and steps as a function of current levels in heart rate and steps. Aim 4 will require depicting each instance in time in terms of risk for being in one of the temporal states associated with subsequent binge eating and/or purging. To do so, we will utilize the posterior probabilities from a latent mixture model where each pattern is differentiated by associations amongst different levels of change. Mixture modeling is a taxonomic approach where timepoints within and between individuals can be grouped together as a function of a model. In this case, the model will differentiate groups of data as a function of the dynamic properties.

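### The watch log does not say whether the reported time is the start or end of an episode and stops at 30 minutes, so Aim 2's pre-event data could include the binge itself

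*Protocol article*

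**What the plan says.** All of this is in the protocol article.

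- **Binge and purge records.** Participants open the watch app "if they have experienced a binge or purge episode" and choose "how long ago it occurred, with response options in five-minute increments ranging from" "Right now” to “30 mins ago". In five-minute steps that is seven options (0, 5, 10, 15, 20, 25, 30). No separate start, end or duration item is described, and no answer beyond 30 minutes.
- **Deep phenotyping (Background).** The app log supplies the event times. Passive patterns are to predict high-risk states "signaling impending binge or purge episodes (time-stamped by active app monitoring").
- **Specific aims, digital longitudinal phenotyping.** Aim 2 is to "Predict the occurrence of binge eating and purging (vomiting) episodes in individuals with BN/BED using passive sensor data".
- **Planned data analysis, digital longitudinal phenotyping aims.** Aim 2 starts by "depicting the dynamics that lead up to a binge or purge event in a multilevel model". No window length or lead time is given for it. Aim 3, in the same paragraph, has a 2-hour post-event window and leaves out data within an hour of a future event.
- **Apple watch.** Heart rate is recorded at about 5-minute intervals.
- **Daily mood and meal records.** Six prompts a day ask, among other things, which behaviors were used. They are not described as giving the time an episode began.

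**The concern.** The article wants to warn people before a binge or purge happens. That requires predictor data from before onset. The only event time described is one self-report whose anchor is undefined and whose range is capped.

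If a participant dates the end of a binge, the whole binge lies before the stamp. If a participant dates the start but reports more than 30 minutes after it, the cap moves the stamp later than the true start. In both cases, heart-rate and step changes produced by the episode could enter the model as its antecedents. Apparent accuracy could rise while true warning time is short or nil. Aim 4 builds on states that precede events, so it would inherit the problem.

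The planned split-half confirmation would not reveal this. Both halves use the same stamping rule, so a model that partly recognizes eating in progress would replicate in both. The validity evidence cited for app logging concerns agreement with retrospective self-report of the behaviors; timing of onset is not mentioned.

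**Working it through.** The article gives no figure for this point, so there is none to reproduce. The check is how much of a pre-stamp window can overlap the binge.

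**From the article:** a lag scale of 0 to 30 minutes, and sensor epochs of about 5 minutes.

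**Assumed, because the article does not give them:** binge duration D of 15 to 120 min, report made r = 0 to 60 min after the binge ends, and predictor window W of 30, 60 or 120 min. Recall is taken as accurate.

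**Formulas.** The binge occupies 0 to D and the report is made at D + r.

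- Recorded time T = (D + r) − min(true lag, 30). The true lag is r if the participant dates the end, and D + r if the participant dates the start.
- Share of the window inside the binge = max(0, min(T, D) − max(T − W, 0)) / W.

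**Results for W = 60 min (12 epochs):**

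| Reading | D | r | T after onset | Share inside binge |
|---|---|---|---|---|
| End | 15 | 0 to 30 | 15 | 15/60 = 25% |
| End | 30 | 0 to 30 | 30 | 30/60 = 50% |
| End | 60 | 0 to 30 | 60 | 60/60 = 100% |
| Start | any with D + r ≤ 30 | | 0 | 0% |
| Start | 30 | 15 | 45 − 30 = 15 | 15/60 = 25% |
| Start | 60 | 0 | 60 − 30 = 30 | 30/60 = 50% (6 epochs) |
| Start | 60 | 15 | 75 − 30 = 45 | 45/60 = 75% (9 epochs) |
| Start | 60 | 30 | 90 − 30 = 60 | 60/60 = 100% |

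**Late logging (r = 60).** For W = 60, 25% to 50% of the window is binge. For W = 30 the share is 0%, but only because the window then lies wholly after the binge, so it is still not pre-onset data.

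**How often the cap could bind.** If the delay from the dated moment to the report were exponential with mean m (an assumption), P(delay > 30) = exp(−30/m): 14%, 37% and 61% for m = 15, 30 and 60 min. If those episodes were still logged at the 30-minute option, each would be stamped m minutes late on average. Averaged over all episodes the lateness is m × exp(−30/m): about 2, 11 and 36 min.

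**What a gap would do.** To keep the window clear of the binge, the gap must be at least T. With r of 30 min or less, T = D under the end reading and max(0, D + r − 30) under the start reading. A 60-minute gap then clears binges up to 60 min under both readings, but not a 120-minute binge dated at its end (T = 120).

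**The case against.** The strongest objection is that a reader might infer more than the text supports.

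- **That onset is never recorded.** The question asked can be understood as referring to the start. On that reading, any episode reported within 30 minutes of onset leaves no binge time before the stamp. The supportable statement is that the anchor is undefined.
- **That logging always follows the episode.** The immediate option allows a report during it, and urges can be logged too.
- **That Aim 2 has no lead-time gap.** The article is silent, which is different from ruling a gap out. Window details are commonly left to a full protocol or analysis plan, which is not shown.
- **That late episodes must be lost or mis-stamped.** The six daily records may pick some of them up, although no onset time is described there. The figure of watch screens is also not shown, so a further timing screen cannot be excluded.
- **That the error has a known size.** No delay or duration data are given. Recall errors can also run early, which would act in the opposite direction.

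All five stand as limits on the claim. The argument is also more direct for binges than for vomiting; for a purge, the risk is mainly that the window holds the preceding binge.

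They do not remove the point. The response scale is a rule of data capture that the article states. A later analysis can add a gap, but it cannot fully recover an onset that was not clearly asked for. Even the favorable reading fails once the cap binds.

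**Conclusion.** The point holds in a limited form. The described log leaves the event time undefined as start or end and offers nothing beyond 30 minutes. Because these stamps define the Aim 2 events, the data before them could include part or all of an episode, which could inflate apparent prediction and overstate warning time.

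The documents do not support the stronger conclusion that Aim 2 would detect eating in progress instead of predicting it. Contamination of a 60-minute window runs from 0% (start reading, reported within 30 minutes of onset) to 100% (for example, a 60-minute binge dated at its end). Where the study falls in that range depends on durations, delays and a window length that the article does not give. The improvement is cheap and should be made.

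**What to change.** **Data capture, for remaining participants**

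- Define the logged time as the onset of the episode.
- Add an item asking when the episode started, and an option to enter a time more than 30 minutes back.
- Flag which version of the log produced each record.

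**Analysis, for all data**

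- End the Aim 2 predictor window a prespecified gap before the recorded time (for example 30 and 60 min), and base the main prediction claim on that lagged result.
- Treat the 30-minute answer on the current scale as 30 minutes or longer.
- Report accuracy by lead time.
- Repeat with prompt reports only (for example 10 min or less). This removes records at the cap, but not the start-or-end ambiguity, so it supplements the gap and does not replace it.

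**Cost.** A small app update and some analysis wording; one extra tap per event; two event-time definitions to handle because recruitment is already under way; and lower stated accuracy at longer lead times.
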